## Abstract

**Background:**

Progression of freezing of gait, a common pathological gait in Parkinson’s disease, is an important risk factor for diagnosing the disease and has been shown to predispose patients to easy falls, loss of independent living ability, and reduced quality of life. Treating Parkinson’s disease with freezing of gait is very difficult, while the use of medicine and operation has been ineffective. Music exercise therapy, which entails listening to music as you exercise, has been proposed as a treatment technology that can change patients’ behavior, emotions, and physiological activity. In recent years, music exercise therapy has been widely used in treatment of motor disorders and neurological diseases and achieved remarkable results. Results from our earlier pilot study revealed that music exercise therapy can improve the freezing of gait of Parkinson’s patients and improve their quality of life. Therefore, we aim to validate clinical efficacy of this therapy on freezing of gait of Parkinson’s patients using a larger sample size.

**Methods/design:**

This three-arm randomized controlled trial will evaluate clinical efficacy of music exercise therapy in improving the freezing of gait in Parkinson’s patients. We will recruit a total of 81 inpatients with Parkinson’s disease, who meet the trial criteria. The patients will randomly receive music exercise with and without music as well as routine rehabilitation therapies, followed by analysis of changes in their gait and limb motor function after 4 weeks of intervention. We will first use a three-dimensional gait analysis system to evaluate changes in patients’ gait, followed by assessment of their limb function, activity of daily living and fall risk.

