## Methods/design

### Trial design

This will be a prospective randomized controlled trial supported by Shanghai Municipal Health Commission. The trial will be carried out at the Shanghai second rehabilitation hospital. Patients who meet our pre-defined eligibility criteria will be randomly divided into three groups, namely music exercise therapy (with routine rehabilitation treatment), exercise therapy (with routine rehabilitation treatment but without music), and control group (with routine rehabilitation treatment only). Patients will be followed up for 3 months and their FOG as well as limb function observed after treatment. A flow chart of the study designed is shown in Fig. 1.

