### Study setting

Research activities will be performed at the Shanghai second rehabilitation hospital, neurological rehabilitation ward.

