### Eligibility criteria

#### Inclusion criteria

Participants that meet the following criteria will be included in the study: (1) clinically diagnosed with Parkinson’s disease [21]; (2) brain computed tomography (CT) and other related imaging scans confirm no brain organic disease; (3) can stand for at least 30 min, with or without auxiliary equipment, and can walk independently for 3 m or more; (4) aged between 40 and 70 years; (5) clinically manifest frozen gait, with stage 2 or 3 Hoehn and Yahr; (6) respond to levodopa or other dopaminergic therapies; (7) exhibit stable condition, clear consciousness, no aphasia, and mental retardation and can understand the content of the scale and cooperate with the examination and treatment; and (8) agree to sign an informed consent form.

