### Recruitment and consent

Recruitment of patients began on June 1, 2020, and will be completed on December 31, 2021, or after the required number is obtained, whichever comes first. If there are not enough participants recruited by the deadline, we will submit an application for extension of time. Participant recruitment will consist of three strategies. Firstly, advertisements will be published on Shanghai Second rehabilitation hospital’s website or other online channels. Secondly, information will be shared via posters displayed in Shanghai Second rehabilitation hospital. Thirdly, recruitment posters will be distributed in nearby communities or primary clinics. Rehabilitation physicians will be requested to provide a list of individuals who meet the aforementioned inclusion criteria, while ineligible ones will be excluded. The study coordinator will invite eligible patients for the trial, by phone. Within 2 weeks of receiving the invitation, patients will receive a telephone call from a research assistant who will provide further information and ask them whether they are interested to participate. Finally, participants who provide a written informed consent and complete the baseline assessment will be randomized into the three groups and subjected to treatments.

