### Adverse event (AE) reporting and harms

Any adverse medical events to the participants will be collected after the subjects have signed the informed consent and agreed to participate in the study. Events will not be considered to be related to music exercise therapy if they occur after the participant has signed the informed consent, but before the intervention. All adverse events occurring after enrolment into the study and before discharge will be recorded and reported to the local Institutional Review Board.

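### The protocol leaves unclear whether people not admitted to the ward may enrol, and it ends adverse-event recording at discharge instead of after a fixed period

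*Protocol article*

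**What the plan says.** Three places in the protocol article describe admitted patients. The abstract (Methods/design) states "We will recruit a total of 81 inpatients with Parkinson’s disease, who meet the trial criteria". Study setting adds "Research activities will be performed at the Shanghai second rehabilitation hospital, neurological rehabilitation ward", and Trial design confirms a single centre: "The trial will be carried out at the Shanghai second rehabilitation hospital". The section on adverse events and harms says "All adverse events occurring after enrolment into the study and before discharge will be recorded" and reported to the review board.

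Recruitment and consent casts a wider net. Of its three strategies, one is online ("advertisements will be published on Shanghai Second rehabilitation hospital’s website or other online channels"), one uses posters inside the hospital, and the last is "Thirdly, recruitment posters will be distributed in nearby communities or primary clinics". Rehabilitation physicians also supply a list of people who meet the criteria. Then "The study coordinator will invite eligible patients for the trial, by phone", and a research assistant telephones again within 2 weeks.

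The 8 inclusion and 7 exclusion criteria cover diagnosis, imaging, walking ability, age, disease stage, drug response, cognition, cooperation and consent. None refers to admission, inpatient status or expected stay.

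Every arm has a fixed course of 5 one-hour sessions a week for 4 weeks. Trial design and Trial status both give a 3-month follow-up.

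**The concern.** The abstract, the setting and the adverse-event rule presuppose a patient in a bed on the ward. The recruitment procedure, with community posters and two phone contacts up to 2 weeks apart, suits people who are at home when first approached. The criteria are what the site will apply at the point of entry, and they do not settle the matter.

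Two things are at stake. The first is whom the result describes: ward patients only, or ward patients together with community attenders. The second, and more concrete, is safety capture. The trial has patients with freezing of gait practise turning, walking in narrow spaces and stair stepping, and the protocol's own background links freezing to falls. Discharge is the only end point given for recording adverse events. A recording period that depends on length of stay gives participants unequal observation. It also makes event counts hard to compare between arms if stays happen to differ.

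**Working it through.** No figure in the plan decides this point, so most of the check sets the sections side by side.

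**1. Who may enter**

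| Section | What it implies about admission |
|---|---|
| Abstract, Methods/design | Inpatients |
| Study setting | Activity takes place on the ward |
| Adverse event reporting | Presupposes a discharge |
| Inclusion and exclusion criteria (8 + 7 = 15 items) | Silent |
| Recruitment: online, communities, primary clinics | Reaches people who are not admitted |
| Recruitment: hospital posters, physicians' list | Can reach inpatients |
| Recruitment: phone invitation and second call | Fits people at home at first contact |

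A community volunteer can satisfy all 15 items. That person belongs to the abstract's population only if admitted, and no section says that recruits from the community will be admitted or for how long.

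**2. The adverse-event window**

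Let L be the time from enrolment to discharge. The stated rule records events from 0 to L. The planned course is 5 × 4 = 20 sessions over 4 weeks.

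- *Discharge at the end of week w, with w below 4, and the course continued afterwards:* the sessions falling outside the window number 5 × (4 − w), which is 15, 10 or 5 for w = 1, 2 or 3.
- *Discharge exactly at week 4:* the course is covered and none of the remaining follow-up is. Three months is 3 × 52/12 = 13 weeks. The article does not say when the 3 months start. Counted from the end of treatment, planned observation is 4 + 13 = 17 weeks, of which 13 go unrecorded and 4/17 = 24% is covered. Counted from enrolment, planned observation is 13 weeks, of which 13 − 4 = 9 go unrecorded and 4/13 = 31% is covered.
- *Never admitted:* L does not exist, so the window has no defined end.

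These cases show what the rule does when followed literally. The documents give no lengths of stay, so they do not estimate how many participants are affected.

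**3. Sample size**

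The plan's 66 evaluable patients reproduce as 22 per arm from a three-arm F test with mean reductions 20.7, 7.9 and 2.6, the largest SD (16.6) used as common SD, two-sided α 0.05 and power 0.912 against the 90% target. For the enrolled number, 66 × 1.2 = 79.2 and 66/0.8 = 82.5, and the stated 81 lies between them. Admission status enters none of these steps.

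**The case against.** The strongest reply is that source of recruitment and place of treatment are different things. A rehabilitation ward can admit people who first heard of the trial from a poster, and the hospital posters and physicians' list can reach patients already there. On that reading the site recruits widely and treats on the ward, and all the sections agree. The abstract also joins inpatient status to the criteria in one sentence, so a person not admitted is arguably excluded already. Cooperation with treatment is an entry condition too, and planned length of stay is a detail that a condensed article may leave to the full protocol.

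Much of this stands. A reader might infer that the trial will enrol a different population from the one stated. The documents show only that it could. Nor is the 4-week course undefined, since every arm specifies it; what is unstated is whether it is delivered during a stay or by attendance. A reader might also want to put a size on imbalance in outpatient share between arms or on loss through early discharge. The documents supply neither an outpatient share nor a discharge rate, so any such figure would be invented.

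The reply does not rescue the adverse-event rule. Even if every participant is admitted, the window follows length of stay, and nothing ties the stay to the course or the follow-up. One could argue that discharge means leaving the trial, but the article does not define it so, and hospital discharge is the natural meaning in a trial of inpatients on a ward. The same section says collection begins after consent, but discharge is the only end it names.

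**Conclusion.** The point holds as an ambiguity with one definite consequence. The protocol does not say whether admission is a condition of entry, and its sections point in different directions. The adverse-event rule, followed literally, gives a window that varies by patient, can close before the course or the follow-up ends, and has no end for anyone not admitted. For a stay that equals the 4-week course, 9 to 13 weeks of planned follow-up go unrecorded, depending on when the 3 months start. This rests on taking discharge to mean discharge from hospital.

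The point does not affect the primary test or the sample size, and it shows no bias in the efficacy comparison. It should be corrected because the correction is cheap and improves the safety data.

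**What to change.** 1. Reconcile the abstract, Study setting, Inclusion criteria and Recruitment and consent. State in the criteria either that admission is required, with a planned stay covering the 4-week course and its assessment, or that outpatients able to attend both may join. In the second case, drop the word inpatients from the abstract and record inpatient or outpatient status at baseline. Describe the population in the report accordingly.
2. In the adverse-event section, replace the discharge limit with one fixed period, the same in all arms, counted from consent or randomisation and covering the course and the planned follow-up. State when the 3 months begin.

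The cost is a wording amendment, which needs ethical review if judged significant, possibly one baseline field on the case report form, and somewhat more adverse-event recording after discharge. If admission is made a condition, a few patients with short planned stays may become ineligible. Recruitment is already under way, so the report should also say which rule applied to patients enrolled before the change.

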**Discussion:**

The findings of this trial are expected to affirm the clinical application of this therapy for future management of the disease.

**Trial registration:**

Chinese Clinical Trial Registry ChiCTR1900026063. Registered on September 20, 2019

## Background and rationale

Parkinson’s disease (PD) is a common neurodegenerative disease in the elderly, which was first described by James Parkinson in 1817. The disease has an incidence of about 1–2% among people aged over 60 years old and is the second most serious neurodegenerative disease in humans [1]. Most PD patients exhibit movement or non-movement symptoms, mainly manifested in intermittent gait restriction or obstruction during walking, especially when turning, walking and avoiding obstacles, which negatively affects their quality of life [2, 3]. The current trend in aging among populations, coupled with the increasing incidence of PD, necessitates development of novel therapies for preventing, treating and delaying progression of the disease [4].

Freezing of gait (FOG) is a common type of pathological gait with disability among patients with Parkinson’s disease during mid and late stages. The condition is characterized by short-term retardation or very short pace, and usually occurs during the start of a step or change of direction [5]. Patients often describe their feet as “stuck” while trying to lift them forward, as if they were stuck to the ground. This process usually lasts for a few seconds [6]. FOG comprises three aspects, namely starting, turning, and walking freezing, and these can occur or be aggravated when a patient faces space obstacles, is under pressure, has low attention, or performs dual tasks. A previous study showed that FOG was the primary cause of walking difficulties in Parkinson’s patients and could cause falls, decreased motor function, and quality of life [7]. Modern therapies for management of Parkinson’s disease have aimed to control symptoms, reduce disability, and improve quality of life [8]. To date, the mechanism of FOG is not clear enough, and this has limited direct and effective treatment the associated symptoms, as well as development of ideal drugs and surgical treatment [9]. In fact, drug therapy has generated little effect on improvement of FOG, while advanced cases have shown very poor response to available drugs [10]. Therefore, drug therapy can only be used as an adjunctive therapy for prevention of FOG.

In the field where traditional medicine has been declared a failure, sometimes music exercise therapy can achieve curative effect. The goal of music therapy is to cause behavioral changes in patients, due to remodeling of brain nerves [11]. Rhythm is an inherent characteristic of music that can associate various behaviors with an external beat and cause synchronization of neural network behaviors [12]. Therefore, music therapists can match music with various behaviors, such as movement, phonation, respiration, and the heart rate, to cause synchronous stimulation of neurons in the brain area. These neurons are responsible for regulating the aforementioned behaviors, strengthening connection of neurons, to generate rapid and long lasting changes in patients [13].

Music intervention is used to improve socialization and cognition and emotion as well as neuromotor function, since it involves various brain regions related to emotion, motivation, cognition, and motor function [14]. In recent decades, numerous evidences have reported efficacy of music intervention, which entails passive, active, improvisational, and combined music therapy, in the clinical environment [15]. Combined music therapy is a kind of special therapy that combines music with other therapies, after integrating the characteristics of music. For example, music exercise therapy, which is a supplement to traditional exercise therapy, combines two kinds of therapies, namely exercise and music therapy. In fact, it is advantageous with regard to simplicity of operation and low cost and hence has a very broad development prospect and application value. Consequently, music exercise therapy plays an active role in treatment of various diseases and has been used to improve patients’ limb motor dysfunction and improve their quality of life [16, 17]. Previous studies have shown that cooperative dance and music training can improve the walking function of patients with Parkinson’s disease and improve their transfer ability [18–20]. However, current researches have mostly adopted a single active or passive application form of music therapy. Moreover, most of the current studies evaluating clinical efficacy of music therapy have focused on subjective indicators, such as changes in scores of the evaluation scale, while ignoring objective indicators that cause low persuasion of the research results. These facts provided rationale for the current study. In our previous study, we found that music exercise therapy could effectively improve the rehabilitation state of patients with stroke, spinal cord injury, Parkinson’s disease, and other nervous system disorders. Overall, these findings indicated that music exercise therapy does not only improve depression and rehabilitation of these patients, but also enhances their limb function, thereby improving quality of their daily life. Since this was a pilot study, it is necessary to validate these findings using a larger sample size and introduce objective observation indicators, such as three-dimensional gait analysis, to affirm the clinical efficacy of music movement therapy in improvement of FOG.

### Trial objectives

The objectives of this trial are:
To validate the therapeutic efficacy of music exercise therapy on FOG as well as motor function and quality of life in Parkinson’s patients.To provide additional evidence on the clinical application of the treatment.

## Methods/design

### Trial design

This will be a prospective randomized controlled trial supported by Shanghai Municipal Health Commission. The trial will be carried out at the Shanghai second rehabilitation hospital. Patients who meet our pre-defined eligibility criteria will be randomly divided into three groups, namely music exercise therapy (with routine rehabilitation treatment), exercise therapy (with routine rehabilitation treatment but without music), and control group (with routine rehabilitation treatment only). Patients will be followed up for 3 months and their FOG as well as limb function observed after treatment. A flow chart of the study designed is shown in Fig. 1.

**Fig. 1 Fig1:**
[figure not shown]
Flow chart of the study

### Study setting

Research activities will be performed at the Shanghai second rehabilitation hospital, neurological rehabilitation ward.

### Eligibility criteria

#### Inclusion criteria

Participants that meet the following criteria will be included in the study: (1) clinically diagnosed with Parkinson’s disease [21]; (2) brain computed tomography (CT) and other related imaging scans confirm no brain organic disease; (3) can stand for at least 30 min, with or without auxiliary equipment, and can walk independently for 3 m or more; (4) aged between 40 and 70 years; (5) clinically manifest frozen gait, with stage 2 or 3 Hoehn and Yahr; (6) respond to levodopa or other dopaminergic therapies; (7) exhibit stable condition, clear consciousness, no aphasia, and mental retardation and can understand the content of the scale and cooperate with the examination and treatment; and (8) agree to sign an informed consent form.

### Exclusion criteria

Participants who meet the following will be excluded from the study: (1) secondary Parkinson’s disease; (2) those with deafness, aphasia, or severe cognitive impairment with difficulty to communicate normally; (3) patients with vascular dementia and frontotemporal dementia; (4) those with intolerance to standard treatment; (5) those who do not cooperate with the study program for rehabilitation; (6) those who have participated in other clinical trials within the past 3 months or are receiving other related treatments midway through the study, which may affect efficacy of this study; and (7) those with a history of neurological deficits other than Parkinson’s disease.

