### Relevant concomitant care permitted or prohibited during the trial

No special provisions.

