### Methods to handle protocol non-adherence and missing data

Analyses will be performed according to the intention-to-treat principle.

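### The exclusion criteria include an event that can only occur after randomisation, and a second one with no time point; removing patients on these grounds conflicts with intention-to-treat

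*Protocol article*

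**What the plan says.** All quotations are from the protocol article.

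- **Exclusion criteria, opening line:** "Participants who meet the following will be excluded from the study".
- **Criterion 5:** "those who do not cooperate with the study program for rehabilitation". No time point is given.
- **Criterion 6, first clause:** "those who have participated in other clinical trials within the past 3 months". This can be established at screening.
- **Criterion 6, second clause:** or who "are receiving other related treatments midway through the study, which may affect efficacy of this study".
- **Inclusion criterion 7** already asks that patients "can understand the content of the scale and cooperate with the examination and treatment".
- **Recruitment and consent:** "participants who provide a written informed consent and complete the baseline assessment will be randomized into the three groups and subjected to treatments". Allocation therefore comes before any study treatment.
- **Data analysis** commits to the intention-to-treat principle. **Methods to handle protocol non-adherence and missing data** gives one rule: "Analyses will be performed according to the intention-to-treat principle".
- **Criteria for discontinuing or modifying allocated interventions** says there are none of a special kind.
- **Relevant concomitant care** reads in full: "No special provisions".

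**The concern.** An eligibility list should contain only facts that can be known before a patient is randomised. Here it also contains something that happens during the trial (other related treatment) and something that may do so (non-cooperation), and the stated consequence of both is exclusion.

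If site staff follow that list, a randomised patient who takes up another treatment, or who stops attending, may be withdrawn and never have the 4-week assessment. An intention-to-treat analysis needs that measurement, and an analysis plan written later cannot recover it.

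The judgement may also be made knowing the arm. Blinding is stated only for the outcome assessor and the data analyst, and the Discussion concedes that blinding therapists and patients is difficult. The amount of programme a patient can fail to follow differs by arm as well: both exercise arms add an hour five times a week for 4 weeks to routine rehabilitation, that is 5 × 4 = 20 extra sessions compared with control. Exclusions could therefore differ between arms for reasons linked to outcome.

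**Working it through.** **1. Timing of each clause**

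| Clause | Can it be known before randomisation? |
|---|---|
| Criterion 6, other trial in the past 3 months | Yes |
| Criterion 6, other related treatment midway | No; it is an event during the study |
| Criterion 5, non-cooperation | Not stated; could be unwillingness at screening or non-attendance later |

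Two facts favour the later reading of criterion 5: the study programme starts after allocation, and inclusion criterion 7 already covers ability to cooperate. They do not settle it.

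**2. Consistency with the other sections**

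Take a randomised patient who starts a related treatment in week 2.

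- Exclusion criteria: the patient leaves the study.
- Discontinuation section: no special criterion applies.
- Concomitant care section: nothing is permitted or prohibited.
- Both analysis sections: the patient is analysed as allocated.

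Nothing says whether this patient is still assessed at 4 weeks or stays in the analysis set.

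**3. The plan's own figures**

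Inputs from Sample size: UPDRS III reductions 20.7 ± 16.6, 7.9 ± 6.3 and 2.6 ± 2.2; two-sided alpha 0.05; power 90%. I take the groups in the order music exercise, exercise, control.

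- One-way ANOVA with three equal groups and SD 16.6 gives 22 per arm (power 0.91): 3 × 22 = 66, as stated.
- 22 × 1.2 = 26.4, rounded up to 27 per arm: 3 × 27 = 81, as stated.

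The present point changes neither figure.

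**4. What differential exclusion could do (illustration on assumed values)**

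Assume no true difference between two arms, normal outcomes with a common SD, and exclusion of a fraction f of patients whose tendency to be excluded correlates ρ with poor outcome. The mean of those kept rises by

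SD × ρ × k(f), where k(f) = φ(z_f) / (1 − f), z_f is the normal quantile at f, and k(0) = 0.

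This gives k(0.05) = 0.109 and k(0.20) = 0.350. The spurious difference is SD × ρ × [k(f₁) − k(f₀)], with the root-mean-square SD of the two arms:

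- music v exercise: √((16.6² + 6.3²)/2) = 12.55
- music v control: √((16.6² + 2.2²)/2) = 11.84
- exercise v control: √((6.3² + 2.2²)/2) = 4.72

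| Contrast (planned difference) | 5% v 20%, ρ 0.3 to 0.7 | 0% v 20%, ρ 0.3 to 0.7 |
|---|---|---|
| Music v exercise (12.8) | 0.9 to 2.1 | 1.3 to 3.1 |
| Music v control (18.1) | 0.9 to 2.0 | 1.2 to 2.9 |
| Exercise v control (5.3) | 0.3 to 0.8 | 0.5 to 1.2 |

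Example: 12.55 × 0.7 × (0.350 − 0) = 3.1 points, which is 3.1/12.8 = 24% of the planned difference.

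A simulation of music v exercise with 27 per arm agrees. The type I error of a nominal 5% t test becomes 5.6% to 9.0% for 5% v 20%, and 6.3% to 13.3% for 0% v 20%. With 20% excluded in both arms by the same process, the mean difference is zero to within simulation error and type I error stays at about 5%.

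**The case against.** Several parts of the opposing case stand.

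- **Not all of criteria 5 and 6 acts after randomisation.** A reader might infer that it does. The 3-month clause is an ordinary baseline criterion. Criterion 5 sits among screening criteria, and the candidates are inpatients on a rehabilitation ward, so unwillingness could be judged before allocation. Its overlap with inclusion criterion 7 proves little, since the two lists overlap elsewhere, for example on aphasia.
- **The text speaks of exclusion from the study, not from the analysis.** The section on non-adherence answers the analysis question with intention-to-treat. A reader might infer a declared breach of that principle. The documents do not go so far; they leave the fate of these patients open.
- **Bias in favour of music exercise therapy is not established.** The music and exercise arms carry the same session load, so the extra hour predicts no difference between those two. For other treatments, control patients might seek them more often, and removing poor responders there would bias against music therapy.
- **No claim about completers or imputation follows.** The section on primary and secondary outcomes does not say that only completers are analysed, and missing-data methods may properly sit in the Statistical Analysis Plan that the protocol promises.

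What the objection does not remove is the second clause of criterion 6. It is explicitly a during-study event with exclusion as its consequence. Deferring to an analysis plan does not help either, because such a plan cannot supply assessments that were never made.

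**Conclusion.** The point holds in limited form and is wrong as written. One clause is a post-randomisation exclusion and a second can be read as one. If they are applied, randomised patients are lost from follow-up or analysis, contrary to the intention-to-treat commitment, and neither clause is reconciled with the sections on discontinuation and concomitant care.

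Bias between arms is a risk that depends on exclusion both differing by arm and being related to outcome. Its direction and size are unknown. The figures above, 0.3 to 3.1 UPDRS III points depending on the contrast, or roughly 5% to 24% of the planned differences, show scale only. They rest on assumed exclusion rates, assumed correlations and a common SD within each pair of arms. They also use UPDRS III, which the protocol borrows for planning because no gait figures were available; the primary outcome is gait.

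**What to change.** 1. Limit criteria 5 and 6 to facts known before randomisation: for example, unwilling to follow the programme, in another trial in the past 3 months, or on related treatment at entry.
2. State that every randomised patient is invited to the 4-week assessment, whether or not sessions were attended or other treatment was taken, and is analysed in the allocated arm.
3. Record later co-treatment and non-attendance as protocol deviations, to be used at most in a per-protocol sensitivity analysis.
4. Reconcile the Exclusion criteria with the sections on discontinuing or modifying interventions, concomitant care, Data analysis, and non-adherence. Which treatments are allowed, and when a patient stops sessions, are clinical matters for the sponsor. The text only needs to separate stopping treatment from leaving follow-up.

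The cost is the rewording of two criteria and one or two added sentences, with ethics review if the change counts as significant. The sample size does not change. The protocol describes recruitment as under way, so the change should be made promptly. The sponsor should also check whether any randomised patient has already been removed on these grounds and, if so, whether that patient can still be assessed.
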